### ACT-Based Intervention plus Activity Tracker WITH Feedback

#### Combining ACT and behavioral change

In the last experimental condition, obese individuals will follow the same rehabilitation program in the inpatient phase of the behavioral change condition, with the addition of four brief ACT sessions of duration 45-min for a total amount of 3 h of one-to-one therapy sessions, exactly as in the ACT condition. In the 16-week outpatient phase, each participant receives feedback from an activity tracker following the same stepped protocol, but messages and feedback are informed by an ACT therapist, including values-based goal setting, the defusion process for difficult thoughts, mindfulness cues, and a set of ACT-consistent metaphors and messages.

Combining ACT, which is a technology itself [50], with an app and wearable technologies is quite innovative. Some commercial apps are already available, but they are not developed in the Italian language.

### Recruitment of the study population, inclusion and exclusion criteria

Inpatients will be eligible when they will meet the following inclusion criteria at the admission to the hospital: (1) age between 18 and 70 years, (2) obesity according to the World Health Organization (WHO) criteria (body mass index (BMI) ≥ 30), (3) provision of written and informed consent to participate, (4) technology friendly to receive feedback through smartphone, e-mail, and wearable devices. Exclusion criteria for the study are the following: (1) other severe psychiatric disturbance diagnosed by the Diagnostic and Statistical Manual of Mental Disorders (DSM-5) that causes functional impairment or might compromise treatment adherence criteria, (2) severe visual difficulties, (3) important limitations of movement in particular subjects for which physical activity is not recommended, (4) concurrent medical condition not related to obesity. DSM-5 [87] will be used as a screening tool for psychiatric disorders. The Medical Ethics Committee of Istituto Auxologico Italiano approved the study protocol and the informed consent process.

### Randomization procedure

Using a double-blind procedure, we will randomly assign all of the participants to one of the four groups. The randomization scheme will be generated using the website Randomization.com (http://www.randomization.com). Randomization and follow-up assessments will be administered by independent practitioners blind to the research hypotheses and condition assignments. The G*Power software (v3.1.9.2) [35, 36] was used to compute the minimum sample size required to conduct this study. All of the participants will be assessed with the Psychological General Well-Being Index (PGWBI) [47, 62, 85] five times: (1) at admission to the clinic, (2) at discharge, (3) at 3 months follow-up, (4) at 6 months follow-up, and (5) at 12 months follow-up. Thus, the *experimental condition* is considered as a between-group variable, and *time* is considered as a within-subject variable. The a priori statistics (partial η^2^ and correlation between measures) were computed by examining previous longitudinal studies using the PGWBI in subjects with obesity [9, 65]. The a priori partial η^2^ was set to assume a value of 0.015 (small effect size) [26, 30], the type I error (α) rate was set at 0.05 (two-sided), the power (1 – β) was set at 0.95 [26], and the a priori correlation between repeated measures was set at 0.50. Finally, sphericity was assumed. G*Power showed that there is a 95% chance to correctly reject the null hypothesis of no significant effect with an overall sample of 168 participants, 42 subjects for each group.

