### Gold Standard Intervention plus Activity Tracker WITHOUT Feedback

#### Medical rehabilitation, motivational support, and psycho-education

During the inpatient phase, participants will participate in the intensive 4-week hospital-based and medically managed rehabilitation program for weight reduction. All patients will be placed on a hypocaloric nutritionally balanced diet tailored to the individual after consultation with a dietitian. Furthermore, they will receive nutritional counseling provided by dietitians, physical activity training provided by physiotherapists, and motivational support with elements of psycho-education provided by physicians trained and informed by psychologists-psychotherapists.

The nutritional rehabilitation program aims to promote change in eating habits and consists of both individual and group sessions twice a week and includes information on obesity and related health risks, setting of realistic goals for weight loss, healthful eating in general, general nutrition and core food groups, weight management, and strategies for preventing relapse. The individual dietary counseling involves evaluation of nutrient intake and adequacy, nutritional and anthropometric status, dietary assessment, eating patterns, history of being overweight, and readiness to adopt change. Another meeting will be scheduled to deliver the activity tracker and linked app. The trackers are presented as mere data collection devices, for medical use only, that do not provide any type of feedback or data to the participants.

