### Gold Standard Intervention plus Activity Tracker WITH Feedback

#### Behavioral change condition with activity tracker

In this experimental condition, participants will be provided the same rehabilitation program for the 4-week inpatient phase as in the control condition. In addition, for these subjects we will implement a stepped protocol using wearable devices/activity trackers to collect information about daily physical activity and providing meaningful and informative feedback. The additional procedure starts during the inpatient phase with delivery and explanation of the use of the wearable devices. In this meeting, longer than the one described for the control condition, experimenters provide information, set individualized goals, and explain the feedback to be delivered by the electronic wearable devices after the end of the inpatient phase. All subjects allocated to this condition will be clustered by date of entrance in the program; then, for each cluster, the length of the baseline phase will be randomly assigned. According to these allocations, the wearable device will start to provide feedback at different times for each participant in the cluster, to directly check the effect of contingent and informative feedback, one of the two independent variables of the study, on the daily level of physical activity, our primary outcome and dependent variable. The stepped protocol includes automatically generated feedback for achieving individualized goals in physical activity or related healthful habits. If the goal is missed one day, a daily report is automatically sent, but if any participant misses repeatedly, the individualized goal researchers provide an individualized contact by text message or e-mail.

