### ACT-Based Intervention plus Activity Tracker WITHOUT Feedback

#### ACT-based intervention

In this experimental condition, the subjects followe the normal medical rehabilitation program described above for the first experimental condition. In addition, within the 4-week period of the inpatient phase, we provide a brief ACT intervention during the hospitalization, followed by consulting/therapy sessions provided by a combination of phone calls, e-mails, and text messages in the outpatient phase. The total duration of one-to-one interventions during the hospitalization is 3 h, with four 45-min sessions during the rehabilitation. For the outpatient phase the ACT intervention includes a monthly 30 min Skype-telephone session, starting after the end of hospitalization, that includes weekly text messages or e-mails but is not linked with any kind of data regarding participants of the study.

The ACT-based interventions include the following: (1) acceptance or “willingness,” which involves the active awareness of difficult private experiences without unnecessary and often dysfunctional attempts to control or avoid unpleasant emotions. “Acceptance” is the alternative to emotional and experiential avoidance. Participants will be trained to improve adherence to a healthful lifestyle by increasing willingness to experience unwanted and difficult sensations and urges while engaging in health-related behaviors. (2) Mindfulness is definable as the process by which we can engage in the present moment, adopting an open and curious attitude. Additionally, mindfulness aims to increase self-awareness by noticing all internal experiences, with a non-judging stance, becoming aware of judgments and being able to let them go. Mindfulness allows one to explore previous control-based attempts to cope with unpleasant thoughts, emotions, and sensations and to demonstrate the ineffectiveness of control while pursuing a meaningful life. (3) With the “defusion” process, participants will be encouraged to alleviate themselves from thoughts and feelings by turning attention toward the “noticing self,” rather than sticking to difficult thoughts. (4) Identification of participant values and related behavioral goals will increase engagement in values-driven behavior, or committed action. Potential barriers to adopting values-driven behaviors and maintaining committed action in the long term will be explored and addressed through metaphors and experiential techniques.

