### Psychotherapists and treatment fidelity

Motivational support and psycho-education will be supervised by experienced and certified psychotherapists from diverse backgrounds with specific training in CBT. The brief ACT intervention will be delivered by two psychotherapists with ACT and CBT background and formal training in ACT. They will receive monthly supervision by senior certified psychotherapists to ensure competent and uniform treatment delivery. A fidelity checklist, checked by a third, blinded therapist, will also be used for both treatments.

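### Assignment is described as double-blind, but participants, therapists and message senders know the condition; only the follow-up assessors and the fidelity rater can be blind, so the self-rated scales are unblinded

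*Protocol article*

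**What the plan says.** All references are to the protocol article.

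- **Randomization procedure.** On assignment: "Using a double-blind procedure, we will randomly assign all of the participants to one of the four groups". On staff: "Randomization and follow-up assessments will be administered by independent practitioners blind to the research hypotheses and condition assignments". The same section bases the sample size (168, 42 per group) on the PGWBI measured five times.
- **Gold Standard plus tracker without feedback.** On what participants are told: "The trackers are presented as mere data collection devices". They are also told that the devices give them no feedback.
- **Gold Standard plus tracker with feedback.** At a longer delivery meeting, "experimenters provide information, set individualized goals, and explain the feedback to be delivered by the electronic wearable devices after the end of the inpatient phase". Researchers later write individually to participants who repeatedly miss their goal.
- **ACT-based arms.** "The total duration of one-to-one interventions during the hospitalization is 3 h, with four 45-min sessions during the rehabilitation". Monthly calls and weekly messages follow in the outpatient phase of the ACT arm without feedback. In the combined arm an ACT therapist shapes the tracker messages.
- **Psychotherapists and treatment fidelity.** "The brief ACT intervention will be delivered by two psychotherapists with ACT and CBT background and formal training in ACT". A third therapist, described as blinded, checks the fidelity list.
- **Hypothesis, goals, and expected results; Assessment procedure.** The primary outcome is physical activity recorded by the wearable. Some other outcomes are self-reported through a web platform. The questionnaires are the PGWBI, IPAQ-SF, AAQ-EX, AAQ-II and a Mediterranean diet score.

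**The concern.** Double-blind normally tells a reader that at least the participant and one other party do not know the treatment. Here the arms differ in things that recipients experience and deliverers do, and no sham or attention control is described. The label therefore states a property that the design does not have.

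Two things are at stake. The first is what can be concluded from the self-rated scales. The PGWBI sizes the trial, and the AAQ-II is both the process that ACT targets and a proposed mediator of well-being. A person who knows they had therapy may answer both differently for that reason alone. The second is assessor blinding, one of the few safeguards this design can have. The sentence on staff puts allocating and assessing in one task list and calls those who do either blind to assignments. It leaves unclear how someone who administers an allocation stays blind to it.

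**Working it through.** **Step 1. Who can be blind, role by role.**

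| Role | What the article describes | Can be blind to condition? |
|---|---|---|
| Participant, ACT factor | Four 45-min one-to-one sessions (4 × 45 min = 3 h), or none | No |
| Participant, feedback factor | Goals set and feedback explained, or told that the device gives none | No |
| ACT therapists | Deliver the sessions; inform messages in the combined arm | No |
| Researchers sending individual messages | Contact those who miss goals in the feedback arms | No |
| Staff administering allocation | Called blind to assignments | Unclear, unless concealment of the next allocation is meant |
| Follow-up assessors | Called blind | Yes, if kept apart from allocation |
| Fidelity rater | Called blinded | Plausibly |
| Analyst | Nothing said | Not stated |

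Presenting the silent tracker as a data collector is the only masking of participants described, and it is partial. It does not hide from them whether they receive feedback.

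**Step 2. Which outcomes assessor blinding protects.** The wearable records the primary outcome, so self-report bias does not apply to it. The five questionnaire measures are answered by participants who know what they received, and a blind administrator does not change that. The article does not say in so many words that the PGWBI is self-completed. This follows from its being listed with the psychometric measures and from the self-report platform.

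**Step 3. The sample size on the PGWBI, reproduced.** Inputs from the Randomization procedure section: partial η² = 0.015, α = 0.05, power 0.95, correlation 0.50, 4 groups, 5 time points, sphericity.

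- f² = 0.015/0.985 = 0.01523, so f = 0.1234.
- For the group-by-time interaction, λ = f² × N × m/(1 − ρ) = 0.01523 × 168 × 5/0.5 = 25.6. The degrees of freedom are 3 × 4 = 12 and 164 × 4 = 656.
- Power at N = 168 is 0.944, against the stated 0.95. The smallest N for 0.95 is 173, within 3% of 168. A partial η² of 0.0154, which rounds to 0.015, gives exactly 168.

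The figure is reproduced within rounding, which confirms that the sizing rests on a self-rated scale. Blinding does not enter the calculation, so N does not change.

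**Step 4. Illustration of a reporting shift.** Assume, with no support from the documents, that knowing the arm shifts answers by δ SD in both ACT arms and that ACT has no true effect. For pooled ACT v no ACT at one time point (2 × 42 = 84 per side), SE = √(2/84) = 0.154 SD. The two-sided rejection probability is Φ(δ/SE − 1.96) + Φ(−δ/SE − 1.96):

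| δ (SD) | δ/SE | Chance of a significant result |
|---|---|---|
| 0 | 0 | 5% |
| 0.1 | 0.65 | 9.9% |
| 0.2 | 1.30 | 25.4% |
| 0.3 | 1.94 | 49.4% |

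The size depends on the test. At δ = 0.2, a four-group ANOVA (λ = 168 × 0.1² = 1.68; 3 and 164 df) gives about 16%. The group-by-time interaction, with the shift at all four post-baseline visits and correlation 0.5 (λ = 2.69; 12 and 656 df), gives about 14%.

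**The case against.** The strongest reply is that the article does not call the whole trial double-blind. The term is attached to the assignment procedure, and the next sentences name independent practitioners as the blind parties. It may therefore mean concealed allocation plus blind assessors. This is a fair reading of intent, and it stands to that extent: nowhere does the article say that participants or therapists are masked, or that results will be presented as double-blind evidence. A reader might infer either from the label, but the text does not go that far. Even so, the label does not ordinarily carry that meaning, and no reading makes participants or deliverers blind.

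Other replies also stand in part:

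- **Role separation.** The staff sentence uses a plural for two tasks. A reader might infer that the same individual allocates and assesses, but the text does not say so. The wording does not exclude it either, and one sentence would settle it.
- **Primary outcome.** The article already makes the tracker measure primary and prefers direct measures to questionnaires. The point does not reach the primary outcome.
- **The false-positive figure.** A reader might take about 25% as a property of this trial. The documents do not support that. The shift is assumed, the statistical analysis section does not name the pooled contrast, and the four-group tests give 14% to 16% for the same shift. Rewording leaves all these figures as they are; they would apply to self-report in any unblinded behavioural trial of this size.
- **Condensation.** An article may leave the details of concealment to the full protocol. Here, however, the issue is a statement that the article makes, not a detail that it omits.

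**Conclusion.** The point holds as a contradiction between the stated blinding and the described arms. Participants, ACT therapists and message senders know the condition. The follow-up assessors and the fidelity rater are the only parties who are both called blind and able to be so. The consequence is limited to the self-rated measures (PGWBI, IPAQ-SF, AAQ-EX, AAQ-II, diet score), which should be read as unblinded self-report. The limitations in the Discussion cover the silent tracker and the small number of inventories but not this.

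The contradiction needs no numerical assumption. No size of bias can be derived from the documents, and the range of 10% to 49% only shows why the label matters. It is worth correcting because the correction is cheap and bears on what may be concluded from the scale on which the trial is sized.

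**What to change.** 1. In the Randomization procedure section, replace the double-blind wording with: *participants, therapists and staff sending messages are not blinded; follow-up assessors and the fidelity rater are.* Name the analyst as blinded only if the sponsor adopts that, since the article does not say so.
2. State that staff who administer the allocation do no follow-up assessment, dividing the tasks among existing staff.
3. Report the questionnaire outcomes as unblinded self-report, and add this to the limitations in the Discussion.

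The cost is protocol wording and a division of existing roles. The sample size does not change. The downside is a more modest claim for the self-reported outcomes.

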### Hypothesis, goals, and expected results

The project aims to promote a long-term change in lifestyle as part of a multidisciplinary intervention, in close collaboration with physicians, the service of clinical nutrition, and osteoarticular rehabilitation.

The main goal of this study is test the efficacy of combining behavioral change technologies through contingent and meaningful feedback provided by wearable devices with an intervention based on ACT, a well-studied psychological treatment developed in a contextual behavioral framework. The combinations of this approach should be feasible and efficient, compared with the gold standard treatment, and have lower costs. Four experimental conditions are provided: (1) usual care during hospitalization with programmed follow-up checks, (2) contingent feedback on daily life activities through activity trackers or stand-alone wearable devices, (3) stand-alone ACT-based intervention, (4) a combination of the previous two conditions: ACT-based intervention and activity tracker with feedback.

The primary outcome, or dependent variable, of the study is level of physical activity as collected by wearable electronic devices, a largely used parameter in scientific investigations [33, 68]. Other outcomes—for example, time of sleep—are collected by wearables, and others are provided by self-report through the web platform. The independent variable of the study is the type of treatment (ACT intervention and feedback provided by activity trackers). For the purpose of the study we collect data about daily steps and a workout log for each participant.

The intervention aims to help people in their everyday environment to more consistently keep the choices they have made and follow appropriate recommendations on diet and movement. The project is directed to participants in the multidisciplinary rehabilitation program at St. Joseph Hospital - Verbania, Istituto Auxologico Italiano, a private research institute that also works for the Italian national health system. The recruitment will take place progressively, and subjects will be randomized to the four experimental conditions set by the protocol. Data will be analyzed in different experimental single-subject over multiple-baseline designs [2, 8]. The subjects are also grouped according to the experimental conditions to allow statistical analysis of experimental intergroup designs, consistent with the approach of a randomized controlled trial (RCT).

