### Assessment procedure

According to the behavioral framework, direct measures are preferred to psychometric inventory when possible. In any case, to deepen the understanding of mechanisms of change, psychometric measures were included. Participants will be asked to complete all study measures before randomization. Follow-up repeated measures assessment will be completed on all study participants 6 weeks later (post-treatment) and at 3, 6, and 12 months follow-up.

Demographic data such as gender, age, marital status, level of education, and employment status will be assessed in order to control for these potential confounders, checking also for biological indicators of risk—obesity, according to WHO criteria, with a BMI of 30 or more [67].

Primary outcome is physical activity as assessed continuously by wearable technology. Activity trackers will collect data, by direct measurement, of daily steps, physical activity, sleep, and food journal with the self-report app connected with the wearable device. Medical data and additional diagnoses (e.g., diabetes) that may confound results will be retrieved from clinical records.

Participants in both groups will provide a history of any psychological treatment or counseling to assess potential familiarity with mindfulness and acceptance-based therapies. A range of physiological and psychological outcome measures will assess the following: modifiable risk factors and recommended lifestyle dietary habits with the Mediterranean Diet Score [73], physical exercise with the International Physical Activity Questionnaire - Short Form (IPAQ-SF) [57] and the Acceptance and Action Questionnaire for Exercise (AAQ-EX) [85]. We also collect data about psychological well-being and quality of life (PGWBI) [47, 62, 85] and psychological flexibility (AAQ-II) [4, 49], a core process directly targeted by ACT interventions and involved as a mediator for well-being [53]. Adjusted change scores for all the outcome measures will be calculated in order to assess the ability of the interventions to produce changes over time.

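### The 168 participants and 95% power are derived for the PGWBI; the stated power does not apply to the primary outcome, tracker-measured physical activity

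*Protocol article*

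**What the plan says.** The protocol article identifies the primary outcome twice in plain terms. Under Hypothesis, goals, and expected results: "The primary outcome, or dependent variable, of the study is level of physical activity as collected by wearable electronic devices". Under Assessment procedure: "Primary outcome is physical activity as assessed continuously by wearable technology". The description of the tracker-with-feedback arm also calls daily physical activity the primary outcome. Steps are among the tracker data: "we collect data about daily steps and a workout log for each participant".

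The sample size is under Randomization procedure. There the PGWBI, given at five visits (admission, discharge, 3, 6 and 12 months), defines the within-subject factor, and the four conditions define the between-group factor. The partial η² and the correlation between measures were "computed by examining previous longitudinal studies using the PGWBI in subjects with obesity". The partial η² "was set to assume a value of 0.015 (small effect size"), the type I error "rate was set at 0.05 (two-sided"), power was 0.95, the correlation 0.50, and sphericity was assumed. The result is 168 participants, 42 per group. It is presented as the minimum number the study needs, with a 95% chance of rejecting the null hypothesis; the sentence names neither an outcome nor a test.

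Under Assessment procedure the PGWBI appears among the further measures: "We also collect data about psychological well-being and quality of life (PGWBI"). The same section says that direct measures are preferred to psychometric inventories where possible.

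**The concern.** A sample-size statement tells the reader what the trial can find on its primary outcome. Here every outcome-specific input (effect size, correlation, number and timing of measurements) belongs to a questionnaire that is not the primary outcome. The article gives no SD, target difference or within-person correlation for steps or any other tracker measure, and no argument that the PGWBI values would hold for them. The data structure differs too: five questionnaire scores against continuous daily recording.

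At stake is the interpretation of the primary result. If the trial finds no difference in physical activity, the protocol as written lets that be reported as a null result from a study with 95% power, and nothing in the article supports that.

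**Working it through.** **1. Reproduce the stated figure.** Inputs from Randomization procedure: k = 4 groups, m = 5 assessments, partial η² = 0.015, ρ = 0.50, α = 0.05, N = 168, sphericity. The article does not name the G*Power test, so each candidate was tried. For the within-between interaction:

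- f² = η²/(1 − η²) = 0.015/0.985 = 0.01523 (f = 0.1234)
- λ = f² · N · m/(1 − ρ) = 0.01523 × 168 × 5/0.5 = 25.58
- df1 = (k − 1)(m − 1) = 12; df2 = (N − k)(m − 1) = 656
- Power from the noncentral F = 94.4%

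The smallest N for 95% is 173 (176 in equal groups). With partial η² = 0.0154, which rounds to 0.015, power at 168 is 95.0%, so rounding explains the gap. The alternatives do not fit:

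| Test, same inputs | Power at 168 | N for 95% |
|---|---|---|
| Condition × time interaction | 94.4% | 176 |
| Between groups | 37% | 684 |
| Within time | 99% | 124 |
| Interaction with λ = f² · df2 | 50% | 432 |

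So 168 and 95% are the figures for the condition-by-time interaction on five PGWBI scores.

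**2. Can the 95% be carried over to physical activity?** The article gives no effect size or correlation for the tracker outcome, so both are assumed here over a range. Same interaction test, N = 168:

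| Partial η² (assumed) | ρ = 0.3 | ρ = 0.5 | ρ = 0.7 |
|---|---|---|---|
| 0.005 | 29% | 42% | 68% |
| 0.01 | 60% | 78% | 97% |
| 0.015 | 82% | 94% | 99.8% |
| 0.02 | 93% | 99% | >99.9% |

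At ρ = 0.5 the N for 95% power runs from 520 (η² = 0.005) to 132 (η² = 0.02). The stated 168 lies inside that span.

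**3. What could be stated for the fixed 168.** The 2 × 2 layout gives 84 v 84 for each factor and 42 v 42 for combined treatment v standard care. Detectable standardised difference d, two-sided α = 0.05, no dropout:

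- Scenario A, unadjusted two-sample t-test at one time point (noncentral t): 0.435 (80% power) and 0.559 (95%) for 84 v 84; 0.619 and 0.796 for 42 v 42.
- Scenario B, baseline-adjusted mean of four post-baseline values, compound symmetry, ρ = 0.5 borrowed from the PGWBI. Variance of the mean of four = (1 + 3 × 0.5)/4 = 0.625. Baseline adjustment removes ρ² = 0.25, leaving 0.375, and √0.375 = 0.612. At 80% power, d = 0.435 × 0.612 ≈ 0.27 and 0.619 × 0.612 ≈ 0.38.

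The method of analysis alone changes the detectable difference by a factor of about 1.6 (1/0.612). To express d in steps per day, multiply by an SD, which the article does not give.

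**The case against.** The PGWBI basis is disclosed in the same paragraph as the 95%, and the arithmetic is sound for it. The article elsewhere calls the trial a small RCT and lists small subgroups as a limitation, so a careful reader would not be misled. The abstract names physical activity and psychological well-being side by side, and the PGWBI is nowhere labelled secondary. The primary outcome also has a second test: baseline length is randomised within clusters in the feedback condition and analysed by a randomization test, which an 84 v 84 comparison does not describe.

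Part of this stands. That the PGWBI is not primary is an inference from physical activity being the only outcome so named. Daily steps are one tracker measure of physical activity, not its definition. The within-person test is a real additional source of information, though it addresses feedback and not the ACT effect. None of it supplies a power figure for the primary outcome, and disclosing the inputs does not limit a conclusion that is worded for the whole study.

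A reader might go further and infer that the trial is underpowered for physical activity, that it can detect only large step differences, or that a corrected power must come out lower. The article does not support this. Those readings need an assumed step SD and the unadjusted single-time t-test of scenario A. The article instead plans adjusted change scores, ANOVA on change and growth curves. The direction of any error is unknown.

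**Conclusion.** The point holds in this form: the 95% power belongs to the condition-by-time interaction on the PGWBI and does not apply to the primary outcome, yet it is stated without that limit as the basis for the trial's size. This rests on the article's own naming of the primary outcome and on reproducing its figure (94.4%, or 95.0% with partial η² of 0.0154). No error is shown in 168 for the PGWBI. For physical activity, power at 168 runs from 29% to nearly 100% over the assumed grid (partial η² 0.005 to 0.02, correlation 0.3 to 0.7), so 168 may be too few or more than enough. The d values are illustrations: scenario A is a conservative benchmark, and scenario B depends on a correlation borrowed from the PGWBI.

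**What to change.** Leave N at 168 and rewrite the sample-size paragraph:

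1. Label the existing calculation as PGWBI, condition by time interaction.
2. Remove the general 95% claim, or restrict it to that test.
3. Add a statement for the primary tracker measure (for example mean daily steps) at the fixed 168: the detectable difference for each factor (84 v 84) and for combined v standard (42 v 42), under the planned baseline-adjusted or repeated-measures analysis. Give the assumed SD and correlation as ranges with their source, and allow for dropout, which the present calculation does not mention.

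The cost is rewording and one added calculation. The trial gives up an unqualified 95% power claim. Design, procedures and recruitment target do not change.
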